#### Safety endpoint measures

The incidences of serious adverse events, drug-related adverse events and mortality from any cause (within 30 days of the time of initiation of therapy) are considered safety endpoint measures of this trial.

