Despite ongoing research on the prevention of postoperative hypocalcaemia, its treatment is well established and uses oral calcium and vitamin D supplementation. Based on empirical evidence, Tartaglia *et al.* [7] were the first to show that routine postoperative administration of calcitriol and calcium salts significantly decreased the risk of severe postoperative hypocalcaemia. Indeed, low levels of vitamin D, as determined by preoperative testing, were shown to be an independent risk factor for postoperative hypocalcaemia [8], suggesting that correction of low vitamin D levels might be a useful measure to reduce postoperative hypocalcaemia rates.

Vitamin D metabolites and analogues are essential in the management of postsurgical hypoparathyroidism. The active form of vitamin D – calcitriol (1,25-dihydroxyvitamin D_3_) – is the preferred clinical option because of its potency and rapid onset and offset of action. Calcitriol regulates the expression of TRPV6, which is a calcium entry channel responsible for calcium absorption in the intestine [9], so that there is a time of onset of action of only some 1 or 2 days compared with 10–14 days for Vitamin D_3_ (cholecalciferol) [10].

We therefore hypothesized that preoperative administration of calcitriol would reduce the rate of hypocalcaemia after total thyroidectomy. Moreover, if postsurgical hypocalcaemia should occur, preoperative vitamin calcitriol prophylaxis should be helpful in reducing the time to manage this condition and thus the duration of hospital stay. So far, and to the best of our knowledge, studies to that effect are still missing.

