### Aim of the study

The overall aim of this study is to evaluate the effect of an early onset of calcitriol supplementation on postoperative hypocalcaemia. This study is specifically designed to evaluate the effects of a preoperative short term administration of calcitriol prior to total thyroidectomy (intervention) in comparison with current standard clinical protocols of postoperative administration of calcitriol in only those patients who have postoperative hypocalcaemia (control group). Calcitriol will be administered according to well-established clinical protocols and no additional diagnostic interventions are intended, in order to reduce the likelihood of adverse events. This study is therefore planned as a post-marketing noninterventional, i.e., observational study. Although we consider HypoCalViD to be an observational trial rather than a prospective randomized controlled trial, because patients are randomly allocated to an interventional and a noninterventional arm prior to surgery, this trial may be attributed a ‘minimal-intervention clinical trial’ as recently defined by EU-directive number 536/2014 of 16 April 2014.

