### Intervention

The specific trial intervention consists of 0.5 μg calcitriol orally, twice a day for 3 days prior to surgery. The control therapy consists of any standard conventional hypocalcaemia therapy according to current guidelines or local clinical standards of the participating clinical centre and adherent to the implemented standards of the respective institution. Standard therapy is defined as the currently accepted and used treatment for this condition, based on the results of past research.

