#### Secondary endpoint measures

Secondary endpoint measures comprise the overall duration of hospital stay, the number of days until restoration of normal serum calcium level, and hospital resource utilization, as well as quality of life and reported patient outcomes.

Duration of hospital stay will be documented according to hospital charts. Prior to and one month after surgery, patients will be asked to complete the well-established SF36 Quality of Life questionnaire [12] and a questionnaire constructed for the assessment of postoperative hypocalcaemia [13]. The number of days needed to adjust hypocalcaemia to a normal level (calcium level = 2.2 to 2.7 mmol/l) will also be assessed.

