## Discussion

Total thyroidectomy is currently the standard surgical procedure for various conditions of the thyroid gland; the aim is to reduce the incidence of recurrent disease and thus avoid re-operations. As a consequence of the more extensive surgical procedure, postoperative hypoparathyroidism is affecting an increasing number of patients. In addition, it has become a burden for the health system, because hypocalcaemic patients require longer in-patient treatment and more medical resources. HypoCalViD has the potential to prove the clinical usefulness of a rather simple intervention with a well-established protocol, commonly used for the correction of postsurgical hypocalcaemia: calcitriol.

A potential weakness of the protocol is that there is neither the patient nor the investigator is blinded. However, as the primary endpoint (serum calcium concentration) is measured using standardized methods and independently of the respective intervention, a placebo effect is unlikely to occur. Secondary endpoint measures, such as the score on the SF36 questionnaire addressing the participants’ quality of life, might also be influenced by the patients’ awareness of having been part of the intervention or control group.

Because this trial aims to address the most common thyroid procedure, i.e., thyroidectomy for benign thyroid conditions, comprising more than 80 % of thyroid procedures, nonbenign reasons for total thyroidectomy were excluded. Patients with malignant conditions often require more extensive resections and might experience hypocalcaemia more often. There might be an even greater effect of calcitriol in these cases. However, these cases only make up for some 5–10 % of all thyroid procedures and the extent of surgery is tailored to the individual patient, making it difficult to study such a heterogenous group.

To obtain a comparable group of postsurgical patients with the same extent of surgical trauma and because a large number of patients is needed to be able to demonstrate a significant effect of the intervention, we decided to exclude malignant deceases for the specific purpose of this study.

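### Non-serious harms count only if labelled drug-related, a label open to every intervention patient but to only about a quarter of controls, so that incidence is not like for like

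*Protocol article*

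**What the plan says.** The section Safety endpoint measures of the protocol article names three measures: "The incidences of serious adverse events, drug-related adverse events and mortality from any cause". A bracket after mortality sets the period: "within 30 days of the time of initiation of therapy". No measure covers non-serious events whatever their cause. The section does not say which drug is meant or who judges relatedness.

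Exposure differs by arm. Under Intervention: "The specific trial intervention consists of 0.5 μg calcitriol orally, twice a day for 3 days prior to surgery". Under Aim of the study, the comparator is "postoperative administration of calcitriol in only those patients who have postoperative hypocalcaemia (control group". Intervention adds: "The control therapy consists of any standard conventional hypocalcaemia therapy according to current guidelines or local clinical standards".

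The Discussion concedes that the trial is open label: "A potential weakness of the protocol is that there is neither the patient nor the investigator is blinded". Its defence covers the laboratory primary endpoint and its caveat covers secondary endpoints such as the SF36. Safety assessment is not mentioned.

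On the upper side of calcium, the Background gives the mechanism: "Calcitriol regulates the expression of TRPV6, which is a calcium entry channel responsible for calcium absorption in the intestine". Secondary endpoint measures gives a normal range: "The number of days needed to adjust hypocalcaemia to a normal level (calcium level = 2.2 to 2.7 mmol/l) will also be assessed". Primary endpoint measure schedules recording before surgery, on postoperative days 1 and 2, at discharge and at day 30 ± 3.

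**The concern.** A drug-related event needs a drug. If most controls never take calcitriol, the same symptom after the same operation can be counted in one arm and not in the other. Where relatedness is judged with knowledge of the allocation, that judgement adds a second source of difference.

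The Discussion says the result is meant to inform whether calcitriol should be recommended for all patients having total thyroidectomy, regardless of vitamin D status. On the planning rates, three quarters of such patients would not become hypocalcaemic without prophylaxis, so even minor harm bears on the balance of benefit and risk. An incidence conditional on the label cannot supply that comparison. With equal true harm and equal attribution among treated patients, it tilts against calcitriol. It could also miss real drug effects that are put down to surgery. Overshoot of serum calcium would be free of the attribution problem, but it is not among the named measures.

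**Working it through.** **Planning figures.** Sample size gives 25 % v 15 %, α 5 % and power 80 %. Two-sided, with pooled variance and no continuity correction:

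n per arm = [1.960·√(2·0.20·0.80) + 0.842·√(0.25·0.75 + 0.15·0.85)]² / 0.10² ≈ 250, or 500 in total, as stated.

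Also as stated, 600 × 0.90 = 540 analysed. These figures are sound. They matter here only because they give the 25 % control rate and the arm sizes under 1:1 allocation.

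**Who can carry the label (drug = calcitriol at any time).**

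| | Intervention | Control |
|---|---|---|
| Randomised, 600/2 = 300 per arm | 300 | 0.25 × 300 = 75 |
| Analysed, 540/2 = 270 per arm | 270 | 0.25 × 270 = 67.5 |
| Not expected to receive calcitriol (of 300) | 0 | 0.75 × 300 = 225 |

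The ratio is 1/0.25 = 4. It assumes that every hypocalcaemic control, and no other, receives calcitriol. If the control rate were the 54 % that the Background cites as the upper end of published reports, the ratio would be 1/0.54 ≈ 1.9. If drug means only the preoperative course, no control can carry the label.

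**What equal harm would look like.** Expected labelled events = 300 × a × s × e, where a is the true non-serious event rate (same in both arms), s is the share of events in treated patients that is called related, and e is exposure (1 or 0.25). The documents give neither a nor s; both are assumptions.

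| a | s | Intervention | Control |
|---|---|---|---|
| 10 % | 5 % | 1.5 | 0.4 |
| 20 % | 10 % | 6 | 1.5 |
| 20 % | 20 % | 12 | 3 |
| 20 % | 30 % | 18 | 4.5 |
| 40 % | 30 % | 36 | 9 |

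The counts change with the assumptions, but the 4:1 ratio does not. Counting all events at a = 20 % gives 60 v 60.

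**The time window.** If therapy means calcitriol:
- Intervention: it starts 3 days before surgery, so 30 days end at about postoperative day 30 − 3 = 27, the early edge of the final visit (30 ± 3). The window includes the operation.
- Control, treated (about 25 %): it starts after surgery. A start on day 1 or 2 (assumed) ends at day 31 or 32. The window excludes the operation.
- Control, not treated (about 75 %): there is no start.

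The bracket may govern only mortality or all three measures; the sentence allows both readings.

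**Raised calcium.** The article has an upper limit of normal (2.7 mmol/l) and scheduled postoperative recording, but the upper limit appears only in the time-to-normalisation endpoint.

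**The case against.** The strongest reply is that this is a condensed article on a short course of an established drug. Definitions of adverse events, causality assessment and the handling of laboratory values normally sit in the full protocol. That holds for those details. It does not cover the choice of endpoint: the article itself fixes drug-related events as the only non-serious measure.

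Data analysis states no safety test, so the incidences may be meant as description. That is fair, and no planned test is claimed here. Two incidences side by side in a randomised trial will still be read as a comparison.

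Four stronger readings are tempting and go beyond the text:
- *Controls are untreated and their cell nearly empty.* Aim of the study and Intervention give controls standard therapy, with calcitriol, when hypocalcaemia develops. A quarter is not nearly none.
- *The whole safety comparison fails.* Serious events and all-cause mortality do not use the label. Readmissions, secondary interventions, length of stay and patient-reported outcomes are also collected in both arms.
- *Unblinded staff assign relatedness.* This is a reasonable inference from the Discussion, but no assessor is named.
- *Raised calcium goes uncounted.* It is not named, but it could enter as a drug-related or serious event.

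It is also right that the preoperative calcium sample is not shown to follow the start of dosing, and that the trial aims to add no diagnostics. A preoperative count may therefore be uninformative.

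**Conclusion.** The point holds in limited form. The non-serious safety incidence is not like for like, because about four times as many intervention patients as controls can carry the label. This 4:1 exposure ratio is the only size the document supports, and it rests on the 25 % control rate with calcitriol given to hypocalcaemic controls. It is not a measured bias. A reader might turn it into a false difference such as 8 % × 1.00 = 8.0 % against 8 % × 0.25 = 2.0 %, but that needs an invented event rate and every event on drug called related.

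Two further faults stand. The window lacks a common start, and this reaches mortality at least and serious events too if the bracket governs all three measures. Raised calcium is also left out of the named measures although the postoperative values are recorded. None of this touches the primary endpoint or the sample size.

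**What to change.** Under Safety endpoint measures:

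1. Make the between-arm measure all adverse events, regardless of judged relatedness. Keep serious events and all-cause mortality, and report relatedness as a descriptive listing by arm.
2. Give all safety measures one window with the same start in both arms: randomisation to the day-30 visit.
3. Add the number of patients per arm with any recorded postoperative serum calcium above 2.7 mmol/l, the limit already given under Secondary endpoint measures. Add a preoperative count only where the sample was taken after dosing began. This is a tabulation threshold and implies no change in management.

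The cost is a wording change, somewhat more adverse-event entry and one extra table from values already recorded. The drawback is that background surgical events will dilute any signal; the descriptive relatedness listing and the calcium table partly offset this.

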#### Economics-based outcome measures

Direct resource use defined by the number of days of in-patient hospital treatment will be documented. Direct medical resource use (direct medical costs) includes the resource use that is an immediate consequence of the disease pattern, such as general and specific clinical diagnostics, medication (in particular vitamin D analogues and calcium supplements), secondary interventions and readmissions. Direct nonmedical resource use is the resource use caused by consequences arising from the postoperative condition, namely the incapacity to work for those who are otherwise in salaried employment.

### Data analysis

The primary hypothesis is that the rate of postoperative hypocalcaemia is lower in the preoperative vitamin D intervention group than in the standard postoperative treatment control group. The secondary hypothesis postulates statistically significant clinical and health economic benefits through the intervention, as compared with the current standard treatment.

The primary effectiveness parameter will be analyzed using a Chi-square test comparing the two groups. Supportive statistical analysis will include logistic regression with factors in the model to include treatment, study centre, age, sex and vitamin D status (appropriate baseline parameters and medical history information may also be considered). The secondary efficacy parameter will be compared between the two treatment groups using a log rank test. In addition, as mentioned, a supportive analysis making use of a Cox proportional hazards regression will also be used, to assess whether there is a difference between treatment groups while accounting for the effect of study centre and other appropriate baseline and medical history parameters. A planned interim analysis will be performed when 270 study participants have completed the study.

The interim analysis will re-evaluate the assumptions made for the study sample size calculation; at this point, the sample size will be re-estimated unless the trial has to be stopped as a result of the interim analysis.

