### Sample size

The sample size has been calculated based on assumptions generated from a critical appraisal of current evidence. According to prior publications, 25 % of the patients in the control group can be expected to develop postsurgical hypocalcaemia as compared with 15 % of the patients in the intervention group. Assuming an α-level of 5 % and a power of 80 %, it is calculated that 500 patients must be recruited to obtain significant results. Assuming a cumulative drop-out rate of 10 %, 700 patients will have to be screened in order to obtain a total number of 600 patients for random allocation. Subsequently, it is expected that data obtained from 540 patients will be analyzed at primary endpoint. By using an adaptive study design, the number of patients will be re-evaluated after the first 270 patients have been treated, with complete follow-up.

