### Randomization

Randomization to the treatment arm and the control group will be performed in a 1:1 ratio, stratified by each participating centre. Random allocation of patients will be dynamical. For the randomization procedure, the computer program ‘Random Allocation Software’ (Version 1.0.0) will be used; permuted block sizes will be 30 and 60.

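### Randomisation is stratified by centre but the primary chi-square ignores centre, so the test is conservative and forgoes some power if hypocalcaemia rates differ between centres

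*Protocol article*

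**What the plan says.** The Randomization section states that allocation "will be performed in a 1:1 ratio, stratified by each participating centre", and that "permuted block sizes will be 30 and 60". The Feasibility section explains why the stratum is the centre and not the surgeon, so centre is a deliberate design factor.

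The Data analysis section then says: "The primary effectiveness parameter will be analyzed using a Chi-square test comparing the two groups". A logistic regression with treatment, centre, age, sex and vitamin D status follows, labelled supportive, and further baseline variables may be considered for it.

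The Sample size section rests on an unadjusted comparison: "25 % of the patients in the control group can be expected to develop postsurgical hypocalcaemia as compared with 15 % of the patients". It continues: "Assuming an α-level of 5 % and a power of 80 %, it is calculated that 500 patients must be recruited". It plans 600 randomised and 540 analysed, with a re-evaluation after 270. The Trial status section reports six centres recruiting.

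**The concern.** Stratified blocks force near-equal arms within each centre, which removes most of the between-centre variation from the treatment comparison. A chi-square on the pooled table still counts that variation in its standard error. If centres have different event rates, the test statistic is too small on average: the test rejects less often than 5% under the null and less often than it could under the alternative.

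There is some reason to expect centre differences. Hypocalcaemia is treated "according to current guidelines or local clinical standards of the participating clinical centre". The endpoint counts a low calcium on any day in hospital, so local testing habits and length of stay could affect the rate. Case mix may differ as well. At stake is some efficiency in the one test that decides the primary hypothesis.

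**Working it through.** **Inputs from the protocol article.** Rates 25% and 15%, α 5%, power 80%, 600 randomised with 10% drop-out (Sample size); 1:1 allocation in blocks of 30 and 60 by centre (Randomization); six centres (Trial status). **Assumed:** a two-sided test, since sidedness is not stated; equal centre sizes of 540 / 6 = 90; and the spread of centre rates, for which the article gives no figure.

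**Step 1: reproduce the sample size.** Without continuity correction, n per arm = [z₀.₉₇₅·√(2p̄(1−p̄)) + z₀.₈₀·√(p₁(1−p₁) + p₂(1−p₂))]² / (p₁−p₂)², with p̄ = 0.20:

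[1.960 × √0.32 + 0.8416 × √0.315]² / 0.01 = (1.1087 + 0.4724)² / 0.01 = 249.98, so 250 per arm and 500 in total, as stated. So 500 is the size for the same unadjusted test.

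Analysed: 600 × 0.9 = 540. Power at 270 per arm = Φ[(0.10 × √270 − 1.1087) / √0.315] = Φ(0.952) = 83.0%.

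**Step 2: size of the pooled test when centres differ.** Let p_k be the rate in centre k under the null, P the mean of the p_k, and W the mean of p_k(1−p_k). With balanced arms in each centre, the variance of the risk difference is (4/N)·W. The pooled chi-square uses (4/N)·P(1−P), and P(1−P) = W + Var(p_k). Hence

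size = 2·[1 − Φ(1.960·√(P(1−P)/W))].

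Six evenly spaced centre rates:

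| Assumed spread | P | P(1−P) | Var(p_k) | W | effective critical value | size |
|---|---|---|---|---|---|---|
| none (25%) | 0.250 | 0.1875 | 0 | 0.1875 | 1.960 | 5.0% |
| 18–32% | 0.250 | 0.1875 | 0.0023 | 0.1852 | 1.972 | 4.9% |
| 10–40% | 0.250 | 0.1875 | 0.0105 | 0.1770 | 2.017 | 4.4% |
| 5–50% | 0.275 | 0.1994 | 0.0236 | 0.1758 | 2.088 | 3.7% |

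The ratio P(1−P)/W cannot be below 1, so with balanced strata the departure can only be conservative.

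**Step 3: power, by simulation.** With six centres of 90 analysed, blocked within centre, and a mean reduction of 10 points, the pooled chi-square falls short of CMH by about 0.1 points (18–32%), 1 point (10–40%: 83.8% v 84.8%) and 2.6 points (5–50%). CMH keeps a size of about 5.0%. With no spread both tests have a size of about 5.0% and power of about 83%.

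**Step 4: a second parametrisation.** Overall rates are held at exactly 25% v 15% and the centre differences are set by an assumed SD on the logit scale (N = 540):

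| logit SD | chi-square size | chi-square power | CMH power |
|---|---|---|---|
| 0.3 | 4.7–5.0% | 83.6% | 83.8% |
| 0.5 | 4.5–4.7% | 83.7% | 84.5% |
| 0.8 | 3.9–4.2% | 84.3% | 86.3% |

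At N = 500 the chi-square power stayed between 80.2% and 81.5% for logit SDs from 0 to 0.8. The power is therefore forgone relative to CMH, and not relative to what was planned.

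**The case against.** The strongest reply is that this is an efficiency preference between two analyses that are both already planned. The plain chi-square is simple, needs no model, is valid and matches the sample-size basis; a centre-adjusted model is prespecified beside it. All of that stands, and it limits the point to a modest one. It does not remove it: the supportive model does not decide the primary hypothesis, its covariate list is left open, and CMH is equally simple and costs nothing when centres do not differ.

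Several stronger readings are tempting and the article does not support them.

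- *The error level is wrong, so the test is invalid.* A reader might infer inflated false positives. The departure is downwards only.
- *The trial is underpowered.* The 500 was computed for this test, and 540 are to be analysed.
- *Centre rates will differ.* The article does not show this. The local standards it mentions concern hypocalcaemia therapy, and the Aim of the study section has controls given calcitriol only once they are hypocalcaemic. That treatment largely follows the endpoint event. Sites are also restricted to high-volume specialist departments and to benign disease.
- *Strong baseline predictors are already in hand and should be in the primary test.* Age and sex are named for the supportive model. Calcium is recorded before surgery, but the Endpoint measures section does not place that sample before the first calcitriol dose. Vitamin D status is in the model, while the Discussion says it is not routinely assessed and that only each site's usual parameters are used.

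**Conclusion.** The point holds as a modest loss of efficiency. The primary test ignores the factor by which patients are randomised. If centres differ, its size falls below 5% (about 4.9% to 3.7% over the spreads examined) and it forgoes about 0.1 to 2.6 points of power against a centre-stratified test. At the low end the difference is negligible. The size rests wholly on the assumed between-centre spread, on six equal centres and on average rates near those planned; the direction rests only on balanced allocation within centres.

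**What to change.** Make a CMH test stratified by centre the primary test. Report a centre-stratified risk difference with its 95% confidence interval as the effect estimate, and keep the plain chi-square as a sensitivity analysis. Fix this before any outcome comparison by arm, including the interim at 270 patients; the trial is unblinded, so the timing should be documented.

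Age and sex may stay in the supportive logistic model. Add preoperative calcium as a covariate only if a value taken before the first calcitriol dose exists, because a later sample is already affected by treatment in one arm.

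The cost is wording in the analysis plan and, since the protocol itself names the chi-square, possibly a protocol amendment. Centre is already known for every randomised patient, so no further data or patients are needed.
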